## Abstract

**Background:**

A major reason for poor childhood vaccine coverage in developing countries is the lack of awareness among parents and caregivers regarding the need for immunization and the importance of completing the entire series of vaccines. Short message service (SMS)–based interventions have been quite effective in different programs such as smoking cessation, treatment adherence, health care scheduled appointment attendance, antenatal care attendance, and compliance to immunization. However, there are limited data from low- and middle-income countries on the role of SMS and automated call–based messages and interventions to improve routine immunization (RI) coverage.

**Objective:**

The primary objective of this study is to evaluate whether automated mobile phone–based personalized messages (SMS or automated call) can improve RI uptake at 6, 10, and 14 weeks of age per the expanded program immunization schedule, compared with a usual care control group. Secondary objectives include assessing the effects of different types of automated SMS text or calls on RI coverage at 20 weeks of age.

**Methods:**

This is a mixed methods study using a clustered randomized controlled trial with 4 intervention arms and 1 control arm, augmented by qualitative interviews for personalizing the message. The study is being conducted in Pakistan (an urban site in Karachi and a rural site Matiari). In Karachi, 250 administrative structures are taken as 1 cluster, whereas in Matiari, a catchment area of 4 Lady Health Workers is considered as 1 cluster. The intervention targets families to receive weekly 1-way or 2-way (interactive) personalized automated SMS or automated phone call messages regarding vaccination. Possible barriers to vaccination are assessed in each family at the time of inclusion to determine the type of personalized messages that should be sent to the family to increase the chance of a positive response. Finally, in-depth interviews using purposive sampling are conducted before and after the trial to determine the family’s vaccination experience and related factors.

**Results:**

All study participants for the cluster randomized trial were enrolled by January 14, 2019. Study exit interviews at 20-weeks follow-up visits will be completed by June 2019.

**Conclusions:**

The results of this study will be useful to understand the respective effects of SMS text messages versus automated phone–based communication to improve RI coverage and timelines. Moreover, information regarding families’ perceptions of vaccination and the daily life challenges for timely visits to the vaccine clinic will be used for developing more complex interventions that use mobile phone messages and possibly other approaches to overcome barriers in the uptake of correct and timely immunization practices.

**Trial Registration:**

ClinicalTrials.gov NCT03341195; https://clinicaltrials.gov/ct2/show/NCT03341195 (Archived by WebCite at http://www.webcitation.org/78EWA56Uo)

**International Registered Report Identifier (IRRID):**

DERR1-10.2196/12851

## Introduction

### Background

Pakistan is one of the countries with the highest rates of child death in the world [1]. It ranks 4th in child mortality, with 60% deaths due to vaccine-preventable diseases (VPDs) [2]. Table 1 [18] shows the current schedule of routine immunization (RI) in Pakistan, which is provided by the government free of cost. The immunization coverage in Pakistan is estimated to be 59%, which is still well below the desired level, leading to continued polio transmission, large measles outbreaks, and thousands of deaths from vaccine-preventable illnesses [2]. In addition, Pakistan is a major polio epidemic country and among 3 countries in the world requiring proof of polio vaccination for international travel [3]. Pakistan demographic and health survey in 2017-2018 suggests 88% percent of children had received BCG vaccine due at birth, 86% and 95% had received the first dose of pentavalent and polio vaccine respectively due at the 6^th^ week. Furthermore, 75% and 86% of children had received the third dose of the pentavalent and polio vaccines, respectively, due at 14^th^ week and measles vaccination was 73%, which is due at 9 months. However, these rates are at 1 year of age and much higher than vaccination coverage rate at scheduled time and among conflict hits and displaced populations [4]. Improved RI coverage is recommended as the priority public health strategy to reduce VPDs and eradicate polio in Pakistan and worldwide.

According to immunization coverage surveys, 1 in 5 children is unimmunized [5]. A major reason for poor childhood vaccine coverage is low immunization uptake, when parents are unable to complete the entire series of vaccines in accordance with the scheduled timelines. Some of the reasons include: (1) the family is not in favor of getting their child immunized, (2) low trust in vaccines provided through Expanded Programme on Immunization (EPI) and government health care providers, and (3) caregivers have forgotten their child’s next vaccination due date or child’s EPI card is misplaced [6]. These barriers may be modified with additional support through education and behavior change strategies. In addition, with more pressing issues of food and shelter, preventive health often takes the back seat, and parents and caregivers forget or ignore the subsequent doses of vaccines for their children. There is an immense need to encourage parents’ care seeking and collaboration with the health care providers to improve initial vaccine uptake and the completion of all doses according to the schedule. New innovative and cost-effective techniques are necessary for practical solutions to improve vaccination uptake and coverage.

Mobile phones offer a new medium to provide education and advocate families or caregivers to enable behavior change so as to improve immunization uptake. Mobile phone use has also increased in countries with low RI coverage and a high risk of VPDs. Good examples are Nigeria and Pakistan, where there were around 170 and 140 million mobile phone subscribers, respectively, in 2014 [7,8]. There is also a surge in use of short message service (SMS), with 237.58 billion person-to-person SMS generated in 2011 estimating to around 175 SMS per mobile phone on a monthly basis in Pakistan [9].

**Table 1 table1:** Childhood immunization schedule for Pakistan.

Disease	Causative agent	Vaccine	Doses	Age of administration
Childhood tuberculosis	Bacteria	Bacillus Calmette-Guerin	1	Soon after birth
Poliomyelitis	Virus	OPV (oral poliovirus vaccine); Inactivated polio vaccine (IPV)	4; 1	OPV0: soon after birth, OPV1: 6 weeks, OPV2: 10 weeks, OPV3: 14 weeks; IPV-1: 14 weeks
Diphtheria, Tetanus, Pertussis, Hepatitis B, Hib pneumonia, and meningitis	Bacteria	Pentavalent vaccine (Diphtheria, tetanus toxoids and pertussis +Hepatitis B + Hib)	3	Penta1: 6 weeks, Penta2: 10 weeks, Penta3: 14 weeks
Pneumonia	Bacteria	Pneumococcal vaccine (PCV)	3	PCVIO 1: 6 weeks, PCVIO 2: 10 weeks, PCVIO 3: 14 weeks
Measles	Virus	Measles	2	Measles1: 9 months, Measles2: 15 months
Diarrhea due to rotavirus	Virus	Rotavirus	2	Rota 1: 6 weeks, Rota 2: 10 weeks

Mobile reminders in the form of phone calls have also proven to be a feasible method of improving RI uptake in resource-limited settings with wide cellphone coverage [10]. A Cochrane review reported that automated telephone communication systems including automated calls are effective in a variety of health care settings such as improving clinic attendance rates, screening, adherence to medications, and laboratory tests [11]. Automated calls were also found to be cost-effective in increasing immunization rates in an urban practice in the United States [12]. A study suggests that mobile phones have wide spread abilities to improve health outcomes in low and middle-income countries (LMICs) by targeting larger populations in a cost-effective manner [13]. Furthermore, SMS-based reminders along with small financial incentives could possibly help in improving RI timelines [14]. Text reminders have also proved to reduce vaccine dropout rate and improve parents’ compliance to immunization-scheduled visits [15,16].

There are limited data from LMICs set up on the role of SMS-based interventions for improvement of RI coverage, and conventional 1-way reminder SMS text messages were used by most of the studies as the intervention [13,21,22]. Overall, very few studies compared reminders, educational, and interactive SMS messages related to childhood vaccination uptake [13,21-26]. Although some of the studies have shown some behavior change for improvement in vaccination coverage, more rigorous application of health behavior change model needs to be applied to understand the impact of reminder, educational, and interactive messages on behavior change related to improvement in RI coverage [17]. However, data from developing countries regarding the role of automated calls in improving vaccine coverage are limited. Majority of the studies have focused on SMS-based intervention.

In this study, we will identify the factors that affect adherence to RI coverage among Pakistani families and caregivers and will examine an important public health question—do low cost, automated SMS text messages and calls improve RI coverage in resource-constrained settings such as Pakistan? In this study, we will compare the effectiveness of different types of messages: reminder, educational, and interactive SMS text messages and automated calls for improving RI uptake. Different types of messages will be developed to meet the possible RI barriers identified; these messages will be sent specifically to the participants according to the type of RI barriers they faced for immunization. This information will be used to develop strategies to improve vaccine adherence in Pakistan.

### Study Objectives

#### Primary

Our first objective is to evaluate whether personalized automated SMS text messages, 1-way versus 2-way, can improve on-time visits at 6, 10, and 14 weeks of age for RI as compared with standard care. Our second objective is to evaluate whether personalized automated calls, 1-way versus 2-way, can improve on-time visits at 6, 10, and 14 weeks of age for RI as compared with standard care. Finally, our third objective is to compare the efficacy of automated SMS text messages versus automated calls on increasing vaccination uptake.

#### Secondary

Our secondary objectives are to learn the perception and attitudes of caregivers regarding childhood vaccination and to find out about factors that might influence mobile phone and SMS text–based interventions for vaccination improvement.

## Methods

### Target Population

Our target population are caregivers of newborn (NB) infants younger than 14 days who are due for their RI at age 6, 10, and 14 weeks according to the EPI schedule of Pakistan.

### Study Goal

Our goal is to identify the barriers faced by families in the uptake of correct immunization practices and to develop adapted messages (SMS or automated calls) to improve vaccine adherence in Pakistan. We will collect information from families regarding perceived sociocultural, technical, and economical barriers that may explain the decrease in vaccine coverage, and possible solutions to overcome these constraints. This information will be used to develop personalized educational messages, reinforced by interactive exchanges (2-way automated SMS and automated calls) with caregivers in the initial 20 weeks of their child’s life.

### Study Hypothesis

Personalized weekly message in the form of automated SMS text message or automated calls according to barriers for RI and language preferences can improve RI uptake according to the schedule for vaccine due at age 6, 10, and 14 weeks as compared with standard counseling by health care providers at EPI center and outreach visits for RI. Interactive voice recording (IVR) or 2-way auto calls might be preferred way of communication to caregivers as compared with other intervention and control for possible improvement in RI coverage and timelines.

### Outcomes

#### Primary

Primary outcomes include: (1) to see a 10% increase in RI through personalized automated mobile phone–based communication (SMS or automated call) at 6, 10, and 14 weeks of age according to the EPI schedule versus standard care; (2) to see a 10% increase in RI within 1 week of the original timeline at 6, 10, and 14 weeks versus standard care; (3) to compare coverage rates of personalized 1-way versus 2-way SMS text messages on improvement in RI at 20 weeks of age; (4) to compare coverage rates of personalized 1-way versus 2-way automated calls on improvement in RI at 20 weeks of age; and (5) to compare coverage rates of personalized SMS text messages and automated calls on improvement in RI at 20 weeks of age. 

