### Analysis of Quantitative Data

Analyses will be conducted according to the intention-to-treat principle, and the Bonferroni correction will be used to control for multiple testing. The primary outcome is to assess difference in vaccination status. Chi-square test will first be used to compare the groups’ percentage. Multivariable logistic regression analyses will be conducted to adjust for confounders. As our randomization unit is cluster-based rather than individual-based, generalized linear mixed effects models or generalized estimating equations models will be employed to account for within-cluster correlation, and hierarchal models will be used. The statistical model for the primary and secondary analyses will be developed as explanatory variables. As secondary analyses of the primary outcome, time-to-immunization curves will be constructed using the Kaplan-Meier method and Cox regression for multivariate analysis.

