### Limitations or Mitigations

We recognize that not all barriers identified are modifiable and amenable to phone calls and SMS text messages. However, most of them reflect a priority ranking that does not favor child routine vaccination. One major reservation about SMS-based interventions is the recipient’s level of literacy. However, there has been mixed input related to the preference of phones calls as compared with SMS text messages in populations of low literacy and resource-constrained settings [20,27]. Mobile phone SMS text messages in local languages, pictorial messages, and in combination with phone calls can further reduce this gap. In our study, we will send messages in local languages (as per the preference of the participants). Although SMS text messages have a limitation of 160 characters and even fewer if translated in other characters, these limitations might help in making the messages simple and brief, especially for populations with low literacy levels [22,28].

The type of intervention will not be blinded, but all families in the same cluster will receive the same intervention. The primary outcome (vaccine completion) is not likely to be influenced by any knowledge of the intervention arm.

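### The 20-week comparisons between message types are secondary in the abstract and primary in the body, and five unranked primary outcomes leave the Bonferroni family undefined; the stated 80% power holds only for one uncorrected pairwise test

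*Protocol article*

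**What the plan says.** **Status of the between-arm comparisons.** The abstract's Objective paragraph states: "Secondary objectives include assessing the effects of different types of automated SMS text or calls on RI coverage at 20 weeks of age". In the body, Outcomes, Primary lists as items 3 to 5: "to compare coverage rates of personalized 1-way versus 2-way SMS text messages on improvement in RI at 20 weeks of age"; "to compare coverage rates of personalized 1-way versus 2-way automated calls on improvement in RI at 20 weeks of age"; and "to compare coverage rates of personalized SMS text messages and automated calls on improvement in RI at 20 weeks of age". Study Objectives, Primary adds: "our third objective is to compare the efficacy of automated SMS text messages versus automated calls on increasing vaccination uptake". The body's secondary objectives and outcomes cover only caregivers' perceptions, barriers and influencing factors.

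**Endpoint.** Primary outcome 1 is an increase in immunization at 6, 10 and 14 weeks according to the national schedule. Primary outcome 2 is "to see a 10% increase in RI within 1 week of the original timeline at 6, 10, and 14 weeks versus standard care". Outcomes 3 to 5 use coverage at 20 weeks. No order of priority is given, and nothing says whether one, any or all of the five must be met. Analysis of Quantitative Data uses the singular: "The primary outcome is to assess difference in vaccination status".

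**Comparisons and multiplicity.** Statistical Analysis describes the main analyses as each of the four intervention arms against control and against one another. Analysis of Quantitative Data names the Bonferroni correction without a family or a number of tests.

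**Sample size.** Sample Size Calculations assumes 30% against 40%, 80% power, alpha .05, ICC .05 and 15 newborns per cluster, giving 615 per arm. It does not say which endpoint or window the 30% refers to.

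**The concern.** A Bonferroni correction has a definite meaning only once the set of primary tests is known. Here the article gives conflicting information on which comparisons are primary and names several endpoints without ranking them, so different sections support different families.

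The endpoints are not interchangeable. A child vaccinated three weeks late but before 20 weeks fails the one-week definition and counts as covered at 20 weeks. The Introduction itself notes that coverage measured at one year is much higher than coverage at the scheduled time.

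Two things are at stake: which result the trial may report as its primary finding, and whether the planned size supports that finding once the promised correction is applied.

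**Working it through.** **Inputs** (Sample Size Calculations and Table 3): p1 = .30, p2 = .40, alpha = .05, power 80%, ICC = .05, cluster size 15, 615 per arm. Two-sided testing is assumed because sidedness is not stated; it reproduces the article's figure.

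**Reproducing the plan's number**
- Per arm under individual randomization, with pooled variance under the null: n = [1.960·√(2·.35·.65) + 0.842·√(.21 + .24)]² / .10² = 355.9, rounded up to 356.
- Design effect: 1 + (15 − 1)·.05 = 1.70.
- 356 × 1.70 = 605.2, which needs 41 clusters of 15 = 615 per arm. Two arms give 82 clusters and 1230 births, as in Table 3.

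The figure of 615 therefore belongs to one two-arm comparison at uncorrected alpha.

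**Power of one arm against one arm under Bonferroni**
- Effective n per arm: 615 / 1.70 = 361.8.
- Standard error under the null: √(2·.35·.65 / 361.8) = .03546. Under the alternative: √(.45 / 361.8) = .03527.
- Power = Φ[(.10 − z·.03546) / .03527], where z is the two-sided critical value at .05/k.

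| Reading of the family | k | alpha per test | z | Power at 615 | Per arm for 80% |
|---|---|---|---|---|---|
| One test, as planned | 1 | .05 | 1.960 | 80.6% | 615 |
| Each arm against control | 4 | .0125 | 2.498 | 62.7% | 870 |
| The five listed primary outcomes | 5 | .01 | 2.576 | 59.7% | 915 |
| All pairs of five arms (5·4/2) | 10 | .005 | 2.807 | 50.5% | 1035 |

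The last column repeats the sample-size formula at the corrected alpha, with the same design effect and whole clusters, before dropout.

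**Comparisons that pool arms** (same design effect, 30% against 40%)
- Four intervention arms against control, 4 × 615 = 2460 against 615: 83.4% with k = 5 and 76.7% with k = 10.
- SMS against calls, 1230 against 1230: 92.2% with k = 5 and 88.2% with k = 10. If the two rates were 40% and 50% instead, 89.5% and 84.6%.

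The loss therefore falls on single-arm contrasts: each arm against control, and 1-way against 2-way.

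**The case against.** The strongest reply is that the body agrees with itself on the between-arm contrasts: the primary objectives, the primary outcomes and Statistical Analysis all treat such comparisons as primary or main, and one abstract sentence is the outlier. A Bonferroni divisor is also commonly left to an analysis plan, and that plan is not shown. Both points stand in part. The abstract may be what needs correcting, and a missing divisor alone would not be a finding. What remains is that the article contradicts itself on primary status and lists five unranked primaries on different endpoints while referring to one primary outcome. The choice of divisor depends on settling that first.

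Several stronger readings are tempting and should not be adopted:
- A reader might infer a family of 9 or 27 primary tests by multiplying ages, definitions and arms. The three ages can equally mean the series due at those visits, so these counts are not the plan's. Nor would power be uniformly low in the 9-test case, because tests of pooled arms against control would keep roughly 78% to 81%.
- A reader might take the 10% increase in outcomes 1 and 2 as an observed-gain threshold, with about 50% power when the true gain is 10 points. No such success rule is stated. The 10 points are the design effect size, and the analysis section specifies tests and models.
- A reader might count "The primary outcome is to assess difference in vaccination status" and the parenthesis in "The primary outcome (vaccine completion) is not likely to be influenced by any knowledge of the intervention arm" as further rival definitions. Both can be read as shorthand.
- A reader might conclude that the arms cannot be ranked because the control and between-arm contrasts use different endpoints. The 20-week survey records vaccination by schedule for every arm, so both endpoints are available for every contrast.
- A reader might say the endpoint and divisor will be chosen after the data are seen. The article shows only that it does not settle them.

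**Conclusion.** The point holds. The 20-week between-arm comparisons are secondary in one place and primary in another, and the primary endpoint and corrected family cannot be derived from the article. The stated 80% power applies to one pairwise test at uncorrected alpha. Under the readings the text allows, power for a single-arm pair is about 63%, 60% or 51%, while the pooled comparisons range from about 77% to 92% at 30% against 40%.

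These figures rest on two-sided testing, the article's own rates, ICC and cluster size, 615 analysed per arm, and divisors of 4, 5 and 10 that are interpretations of the text. The size of the loss is therefore conditional on the family chosen; the contradiction in primary status is not.

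**What to change.** Before analysis, and with a date:
1. Name one primary endpoint with one fixed timing window, use it for all primary contrasts, and state which window the 30% control rate refers to. Make the other endpoints secondary.
2. List the contrasts in the primary family to which the Bonferroni correction applies.
3. Reconcile the abstract, Study Objectives and Outcomes on the between-arm 20-week contrasts. Either status is acceptable if fixed in advance.
4. Restate the power at the resulting Bonferroni alpha, separately for single-arm and pooled contrasts.
5. Move the 10% increase from the outcomes to the sample-size assumptions, worded as absolute percentage points.

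The cost is wording only; no new data are needed. The downside is fewer claims labelled primary and, for single-arm contrasts, a stated power below 80% if more than one primary test is kept.

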#### Sample Size Calculations

Assumptions used for calculating sample size are as follows: increase in coverage rate from 30% to 40%, having a power of 80% with an alpha error at .05. The sample size per arm would be 615 per arm or 3075 for all 5 arms. Adding a 10% dropout will make it 677 per arm or 3385 recruitment for all 5 study arms. The ICC is taken as .05, with an estimate of 15 NB per cluster (see Table 3).

**Table 2 table2:** Cluster randomized clinical trial.

Study arm	Automated SMS^a^ text and phone calls			
	1-way SMS text	2-way SMS text	1-way phone calls	2-way phone calls
1	X^b^	—^c^	—	—
2	—	—	X	—
3	—	X	—	—
4	—	—	—	X
5	—	—	—	—

^a^SMS: short message service.

^b^Applicable.

^c^Not applicable.

**Table 3 table3:** Sample size calculation. Having a difference of 10% and the sample size given (ie, 1230 is 2 groups, 1:1) in our study, we have 5 groups (615x5)+10% dropout=3385.

Serial #	Interclass correlation	Range of cluster size					
		Cluster size of 15		Cluster size of 20		Cluster size of 30	
		Clusters, n	Total birth required, n	Clusters, n	Total birth required, n	Clusters, n	Total birth required, n
1	0.01	54	810	44	880	32	960
2	0.05	82	1230	70	1400	58	1740
3	0.09	108	1620	98	1960	86	2580
4	0.1	114	1710	104	2080	94	2820
5	0.13	134	2010	124	2480	114	3420
6	0.15	148	2220	138	2760	128	3840
7	0.2	180	2700	172	3440	162	4860
8	0.21	188	2820	178	3560	168	5040
9	0.25	214	3210	206	4120	196	5880
10	0.3	248	3720	238	4760	230	6900
11	0.35	280	4200	272	5440	264	7920
12	0.37	294	4410	286	5720	278	8340
13	0.4	314	4710	306	6120	300	9000
14	0.45	346	5190	340	6800	334	10,020
15	0.5	380	5700	374	7480	368	11,040

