### Statistical Analysis

Analyses will be conducted according to the intention-to-treat principle. When the information cannot be gathered, the vaccine status of the child will be *failure* (conservative approach). Missing the vaccine EPI card to verify vaccine status at home will lead to a deeper investigation in the family and also the vaccine clinic. From previous experience, we expect this process to be successful in identifying the outcome of over 95% (95/100) of the children who remain in the study at 20 weeks. Families that have left the study for any reason (moving, withdrawal, child death) will be interviewed (if possible) and the information gathered used for the outcome classification. If the information is not clear or incomplete, the child’s status regarding vaccination will be *failure*.

The main analyses will be comparing our 4 study intervention arms against the control, and with each other. For the purposes of our study, we will compare each of the 4 interventions with each other and with the control arm. For example, 1-way versus 2 SMS, reminder versus educational SMS, 1-way reminders SMS versus control, 1-way educational SMS versus control, 2-way reminders SMS versus control, 2-way educational SMS versus control, 2-way education versus 1-way reminder, and 2-way reminder versus 1-way educational.

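### SMS versus calls is a primary question about mode, but the plan describes only arm-against-arm comparisons and gives no power for any contrast between active arms

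*Protocol article*

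**What the plan says.** The Intervention Group section says that SMS and calls share content and interactive features and differ only in how they are delivered. With Table 4, this makes the four active arms a 2x2 layout: mode (SMS, call) by interactivity (1-way, 2-way).

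Three of the five primary outcomes in the protocol article compare active arms:

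- Outcome 3: "to compare coverage rates of personalized 1-way versus 2-way SMS text messages on improvement in RI at 20 weeks of age".
- Outcome 4: "to compare coverage rates of personalized 1-way versus 2-way automated calls on improvement in RI at 20 weeks of age".
- Outcome 5: SMS against automated calls, worded by mode, with no restriction to 1-way or 2-way arms. The third primary objective is worded the same way.

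On the analysis, the Statistical Analysis section says "we will compare each of the 4 interventions with each other and with the control arm". Its examples are all pairwise. No pooled or factorial contrast appears there or under Analysis of Quantitative Data, which adds a Bonferroni correction and a mixed or GEE model for clustering.

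The sample size assumes "increase in coverage rate from 30% to 40%, having a power of 80% with an alpha error at .05". The table note makes clear that this is one two-group comparison ("1230 is 2 groups, 1:1"), then repeated for five arms. No target difference is given for any comparison between active arms.

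**The concern.** Outcome 5 asks about mode. If it is answered by pairs of arms, each test uses two of the four active arms, and the single question of SMS versus calls breaks into several answers that may disagree. The general question of whether interactivity helps has no overall estimate at all, because it is split across outcomes 3 and 4.

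A reader who sees 80% power in the sample size section may assume that it applies to every primary outcome. It was calculated for one active arm against control at an unadjusted .05. The Conclusions of the abstract name the respective effects of SMS and automated calls as what the study should clarify, so the precision of that contrast matters for how the result is used.

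**Working it through.** **Inputs.** From Sample Size Calculations: 30% versus 40%, power 80%, alpha .05 (sidedness is not stated; two-sided is assumed and reproduces the figure). "The ICC is taken as .05, with an estimate of 15 NB per cluster". "The sample size per arm would be 615 per arm or 3075 for all 5 arms". The recruitment figure of 677 is 615 x 1.10; the 615 is used here, as the plan uses it for power.

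**Assumption.** The documents set no difference between active arms. I take 40% in the poorer active arm, which is the plan's own target against control, and show gaps of 5, 7.5 and 10 points.

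**Step 1: the plan's figure.** For two proportions with pooled variance under the null:

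n = [1.960 x sqrt(2 x .35 x .65) + 0.842 x sqrt(.30 x .70 + .40 x .60)]² / .10² = 356 per arm.

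Design effect = 1 + (15 - 1) x .05 = 1.70. Then 356 x 1.70 = 605.2, rounded up to 41 clusters of 15 = 615 per arm, 82 clusters and 1230 for two groups. This matches the plan exactly. At 615 per arm the power for 30% versus 40% is 80.6%.

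**Step 2: power of a contrast.** With effective size m = n / 1.70 per side:

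power = Φ{ [d x sqrt(m) - z x sqrt(2p(1 - p))] / sqrt(p1(1 - p1) + p2(1 - p2)) },

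where d = p2 - p1 and p is the mean of p1 and p2. A single pair has m = 615 / 1.70 = 361.8. Two arms pooled per side have m = 1230 / 1.70 = 723.5. Each cluster belongs to one arm, so the design effect is unchanged.

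Example, 40% versus 50% at .05:

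- Single pair: (.10 x 19.02 - 1.960 x .7036) / .70 = 0.747, so 77%.
- Pooled: (.10 x 26.90 - 1.960 x .7036) / .70 = 1.873, so 97%.

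**Step 3: results.** The plan does not state the number of tests in the Bonferroni family. I show 5 (the primary outcomes, .01) and 10 (all pairs of five arms, .005). Each cell is single pair, then pooled; the pooled figures assume no mode-by-interactivity interaction.

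| Alpha | 40 vs 45% | 40 vs 47.5% | 40 vs 50% | Detectable at 80% power (points) |
|---|---|---|---|---|
| .05 | 27%, 49% | 53%, 82% | 77%, 97% | 10.4, 7.3 |
| .01 | 11%, 26% | 29%, 62% | 55%, 90% | 12.7, 8.9 |
| .005 | 7%, 19% | 22%, 53% | 46%, 85% | 13.5, 9.5 |

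**Step 4: what an interaction does.** Suppose that three active arms reach 40% and 2-way calls reach 50%. Pooled 1-way versus 2-way is then 40% versus (40 + 50)/2 = 45%, with 49% power at .05 and 19% at .005. The within-call pair of outcome 4 remains 40% versus 50%, with 77% and 46%. Pooled SMS versus calls is diluted in the same way, to 40% versus 45%.

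**Step 5: precision of the interaction.** If v is the variance of one arm's rate, a single pair has variance 2v, a pooled contrast 4v/4 = v, and the interaction (difference of differences) 4v. Its standard error is therefore sqrt(2) times that of a pair, so the detectable interaction is roughly 10.35 x 1.414 = 14.6 points at .05.

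**The case against.** Four points on the other side carry weight.

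*Outcomes 3 and 4 are proper questions.* The objectives keep SMS and calls apart, and whether interactivity helps within each mode is a legitimate simple effect. A reader might infer that these comparisons throw away half the data. The documents do not support that: SMS children inform the effect of interactivity in calls only if there is little interaction. The Study Hypothesis singles out 2-way calls as possibly preferred, and Step 4 shows that pooling loses power under that pattern. This stands, and it rules out replacing outcomes 3 and 4.

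*SMS versus calls may already be meant as pooled.* Outcome 5 is worded by mode and the pairwise list is given as examples, so a reader who concludes that the plan fixes this contrast as single-arm pairs goes too far. Still, the only analysis described is pairwise, so the text needs to say which applies.

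*The power is not poor under every assumption.* A reader might infer that the active-arm contrasts are badly underpowered. For 10 points, the only difference that the plan names, an unadjusted pair has 77%, just short of 80%. The low figures come from smaller gaps, which are my assumption, or from the Bonferroni correction, which is absent from the sample size and also lowers one active arm versus control (30% versus 40%) from 80.6% to 59.7% at .01 and 50.5% at .005. Pooling does not rescue a 5-point gap. Nor is an equivalence claim planned, so a null result being read as one is a risk of interpretation and not a stated aim.

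*Contrast coding often sits in the analysis plan.* True, and the planned models can carry a pooled contrast. But this article itself names the contrasts as primary, describes their analysis and gives a power statement, so it can be corrected on those points. The Abstract also places the comparison of message types among the secondary objectives; that status should be settled.

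**Conclusion.** The point holds as a mismatch between questions and analysis, of moderate weight. The active arms form a 2x2 layout and outcome 5 is a question about mode, yet the plan describes only arm-against-arm comparisons and sizes none of the contrasts between active arms.

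Pooling lowers the detectable difference by about 3 points at .05 and 4 points at .005. A single pair under Bonferroni for 10 tests needs 13.5 points, more than the 10-point gain planned over control.

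These figures rest on 40% in the poorer arm, equal clusters of 15, ICC .05, 615 evaluable children per arm and, for the pooled values, little interaction. The conclusion does not extend to calling outcomes 3 and 4 wrong.

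**What to change.** 1. Analyse outcome 5 as one pooled contrast, both SMS arms against both call arms, adjusted for interactivity, in the cluster-adjusted model already planned.
2. Keep outcomes 3 and 4 as within-mode comparisons.
3. Add a pooled 1-way versus 2-way contrast, adjusted for mode, and report the mode-by-interactivity interaction with its confidence interval. Given Step 5, a non-significant interaction should not be taken as evidence that there is none.
4. State that the 80% power covers one active arm versus control at unadjusted .05. Define the Bonferroni family and give the detectable difference for each active-arm contrast under it.
5. Reconcile the arm numbers before contrasts are coded: Table 2 has arm 2 as 1-way calls and arm 3 as 2-way SMS, and Table 4 has the reverse.

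Cost: no additional participants or data. The pooled effects average over any interaction, which the Study Hypothesis makes plausible, and one added contrast enters the multiplicity family. The article reports that enrolment has closed, so the change should be dated and recorded before outcomes are compared by arm.
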